### Randomization

The role of randomization in an HSW trial is to determine which clusters will permanently enroll in the control group, which will enroll permanently in the intervention group, and the order in which the others will transition from control to intervention (Fig. 1c). Although the analysis will control for each individual unit, randomization occurs at the hospital level as opposed to the unit level to prevent the possibility of contamination. If units within a hospital were allowed to transition at different times, the intervention in one unit might inadvertently influence outcomes in the other, nontransitioned unit. One way that contamination could happen is through staff members from a transitioned unit temporarily working a shift in the nontransitioned unit. Therefore, when multiple units from a hospital are participating in the trial, all units are assigned the same transition date, reducing the possibility of contamination.

All possible permutations of the hospitals were considered for the order in which hospitals would transition from control to intervention. However, some permutations lead to a transition schedule in which the smallest hospitals transition early and the largest hospitals transition late, causing more subjects to be enrolled in the control group than in the intervention group. The imbalance for each permutation was estimated on the basis of hospital-specific enrollment expectations, and permutations with excessive imbalance were excluded. The permutation selected for implementation was then chosen at random from permutations with adequate balance with respect to expected enrollment between intervention and control groups.

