### Sample size calculation

In the single-center pilot, the intervention was associated with an increase in survival with favorable neurologic outcome from 29% to 50% (21 percentage points). We anticipate that we will see improvement to a rate similar to that achieved in the single-center pilot, but preliminary data from another study show that CPCCRN hospitals have a higher average baseline rate of survival with favorable neurologic outcome than the single-center pilot [34]. Therefore, our goal was to select a design and sample size that would provide approximately 80% power (at a significance level of α = 0.05) to detect a more conservative increase from 40% to 51% in survival with favorable neurologic outcome. An important factor for sample size calculation in cluster-randomized trials is the intracluster correlation (ICC), a measure of the similarity in outcomes among patients in the same cluster compared with outcomes among patients in different clusters [35]. The ICC was assumed to be 3% on the basis of pilot data from the multicenter Therapeutic Hypothermia after Pediatric Cardiac Arrest In-Hospital Trial [36].

The power and sample size estimates used for planning this trial were based on the method introduced by Hussey and Hughes [37], though generalized to allow for transition periods and implemented in PASS version 15 software [38]. This method uses a Wald Z-test to evaluate a null hypothesis of no effect against a two-sided alternative. We considered several trial design configurations, including parallel group, TSW, and HSW designs. We also investigated the impact of transition duration. With an ICC of 3%, an HSW design was found to be optimal (Table 2) [21, 39]. Long transition periods in HSW and especially in TSW designs increased the trial duration necessary to achieve > 80% power (Table 2). Therefore, an HSW design was selected with short (3-month) transitions.

**Table 2 Tab2:** Required duration of enrollment to achieve > 80% power

	Duration of enrollment (years)^a^
Trial design	
Parallel	NA^b^
Traditional stepped-wedge	
6-month transition	6
3-month transition	5.25
Hybrid stepped-wedge	
6-month transition	4.75
3-month transition	4.5

^a^Duration of enrollment is the approximate number of years required to achieve > 80% power to detect an increase from 40% to 51% in the rate of survival with favorable neurologic outcome

^b^In this context, a parallel design cannot achieve 80% power, regardless of the duration of enrollment

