To estimate power for the HSW design, we assume that two hospitals, each with two units, are randomly assigned to begin with the intervention, and similarly that four units at two hospitals are assigned to remain as control hospitals for the duration of the study. Enrollment was assumed to be evenly distributed across the 18 units and also across the 18 time periods. A 3-month transition period was included for each of the ten transitioning units in the design-pattern matrix (Table 3). Units are the clusters used for sample size calculations and planned analyses. However, as noted above, randomization occurs at the hospital level to minimize the possibility of intervention contamination between units within a hospital. We found that analyzing 1256 index events (4 per unit per period) would provide 77% power to detect an 11-percentage-point increase in the rate of survival with favorable neurologic outcome from a baseline rate of 40%. Power increases to 84% when analyzing 1570 index events (5 per unit per period). On the basis of concavity of the power curve, analyzing 1391 subjects provides > 80% power. On the basis of historical CPR rates in participating units, we anticipate enrolling 1540 index events over the 4.5-year enrollment period. An estimated 48 index events will occur during the transition periods, allowing analysis of the remaining 1492 events and providing > 80% power.

**Table 3 Tab3:** Design-pattern matrix for sample size calculations in a 4.5-year hybrid stepped-wedge design with 3-month transitions

Unit	Time period (18 × 3 months)																	
	T1	T2	T3	T4	T5	T6	T7	T8	T9	T10	T11	T12	T13	T14	T15	T16	T17	T18
1	0	0	0	0	0	0	0	0	0	0	0	0	0	0	0	0	0	0
2	0	0	0	0	0	0	0	0	0	0	0	0	0	0	0	0	0	0
3	0	0	0	0	0	0	0	0	0	0	0	0	0	0	0	0	0	0
4	0	0	0	0	0	0	0	0	0	0	0	0	0	0	0	0	0	0
5	0	0	0	0	0	0	0	0	0	0	0	0	0	0	0	.	1	1
6	0	0	0	0	0	0	0	0	0	0	0	0	0	0	0	.	1	1
7	0	0	0	0	0	0	0	0	0	0	0	0	.	1	1	1	1	1
8	0	0	0	0	0	0	0	0	0	0	0	0	.	1	1	1	1	1
9	0	0	0	0	0	0	0	0	0	.	1	1	1	1	1	1	1	1
10	0	0	0	0	0	0	0	0	0	.	1	1	1	1	1	1	1	1
11	0	0	0	0	0	0	.	1	1	1	1	1	1	1	1	1	1	1
12	0	0	0	0	0	0	.	1	1	1	1	1	1	1	1	1	1	1
13	0	0	0	.	1	1	1	1	1	1	1	1	1	1	1	1	1	1
14	0	0	0	.	1	1	1	1	1	1	1	1	1	1	1	1	1	1
15	1	1	1	1	1	1	1	1	1	1	1	1	1	1	1	1	1	1
16	1	1	1	1	1	1	1	1	1	1	1	1	1	1	1	1	1	1
17	1	1	1	1	1	1	1	1	1	1	1	1	1	1	1	1	1	1
18	1	1	1	1	1	1	1	1	1	1	1	1	1	1	1	1	1	1

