### Statistical analysis

The primary analysis is to assess the effect of the intervention on survival with favorable neurologic outcome. This analysis is based on subjects enrolled during the control period or the intervention period and excludes subjects enrolled during the transition period. Secondary events (after the first eligible CPR event) during the hospitalization are excluded. The effect of the intervention will be assessed with the following test of hypothesis:H_0_: The intervention does not affect the rate of survival with favorable neurologic outcome.H_1_: The intervention increases or decreases the rate of survival with favorable neurologic outcome.

Survival with favorable neurologic outcome will be the outcome for a multivariable logistic regression model. The primary predictor in the model will be treatment group (intervention vs. control). Fixed covariates in the model will be age category (≤ 6 months, > 6 months), Pediatric Risk of Mortality score (PRISM; a measure of illness severity in the 2–6 h prior to CPR) [40], first documented rhythm, illness category (medical cardiac, surgical cardiac, medical noncardiac, surgical noncardiac), and a piecewise linear spline of time. Age, illness category and severity, and first documented rhythm are known predictors of mortality and are included to improve the model fit and potentially increase power. In contrast, survival with favorable neurologic outcome is not expected to change over time. However, without adjusting for time, an improvement over time in survival with favorable neurologic outcome that is unrelated to the intervention would be erroneously interpreted as evidence for the intervention owing to the increased enrollment in the intervention group toward the end of the trial. Including time as a covariate is critical for TSW and HSW designs in order to have valid inference in case of potential temporal trends. Although time is often modeled as a categorical variable in TSW trials, we chose to model time as a piecewise linear spline because we expect it to provide better model fit with fewer estimated parameters. For the spline, knots will divide the enrollment period into epochs of equal duration. The number of knots will be chosen to minimize the Akaike information criterion. There are 18 distinct units at the 10 participating hospitals. Unit will be included as a random effect to account for variability in outcomes between units and increase the generalizability of results.

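### Hospitals are randomised but the primary model has a random effect for unit only, so the 5% test is too liberal if outcomes correlate within hospitals

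*Protocol article*

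**What the plan says.** The Randomization section states that "randomization occurs at the hospital level as opposed to the unit level to prevent the possibility of contamination". Where a hospital contributes several units, "all units are assigned the same transition date, reducing the possibility of contamination". The randomised cluster is therefore the hospital.

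The Sample size calculation section then states: "Units are the clusters used for sample size calculations and planned analyses". The Statistical analysis section notes that "There are 18 distinct units at the 10 participating hospitals" and specifies one random effect: "Unit will be included as a random effect to account for variability in outcomes between units and increase the generalizability of results".

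No section adds a hospital effect, a variance estimate that is robust at hospital level, or a small-sample correction. The ICC is a single figure, 3%, with no split between hospital and unit. For planning, each fixed arm is taken as two hospitals with two units each ("two hospitals, each with two units, are randomly assigned to begin with the intervention"). The other ten units belong to the six hospitals that cross over.

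**The concern.** A random intercept for unit assumes that two units in one hospital are no more alike than two units in different hospitals. Because those units always share an allocation, any hospital effect moves them in the same direction within the same arm. The unit-only model counts them as separate replicates of the comparison.

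The hybrid design is more exposed than a traditional stepped wedge. Four hospitals never cross over, and their contribution to the treatment contrast depends on comparing hospitals. Under the planning assumption, that part of the comparison rests on four randomised hospitals but is counted as eight units.

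If a hospital component exists, the error has one direction: the interval is too short and a true null is rejected too often.

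**Working it through.** **Inputs from the protocol.** Table 3 matrix: 18 units by 18 periods, less 10 transition cells, which leaves 324 - 10 = 314 cells. Rates 40% and 51%, ICC 0.03, two-sided Wald Z at 0.05, 1492 events analysed.

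**Assumptions not in the protocol.**
- The share *w* of the between-unit variance that is common to the units of one hospital, range 0 to 1.
- Eight two-unit and two one-unit hospitals (8 × 2 + 2 × 1 = 18). The one-unit hospitals are among those that cross over (4 × 2 + 2 × 1 = 10 units). Table 3 has five steps of two units, so the two one-unit hospitals are placed at the same step.

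**Step 1: reproduce the stated power.** Generalised least squares after Hussey and Hughes, with categorical periods and a random unit effect:
- Within-unit variance 0.97 × 0.24 = 0.2328; between-unit variance 0.03 × 0.24 = 0.0072.
- SE = square root of the treatment element of (X′V⁻¹X)⁻¹; power = Φ(0.11/SE - 1.96).

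| Events | SE | Power | Protocol |
|---|---|---|---|
| 1256 | 0.0406 | 77.3% | 77% |
| 1391 | 0.0391 | 80.3% | > 80% |
| 1492 | 0.0381 | 82.2% | > 80% |
| 1570 | 0.0374 | 83.6% | 84% |

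The calculation matches the plan. Other variance conventions give about 80% to 82% at 1492 events.

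**Step 2: size of the unit-only test, variances known.** Let R be the true SE (hospital plus unit covariance) divided by the SE that the unit-only model reports. True size = 2Φ(-1.96/R). The ranges cover different positions of the one-unit hospitals.

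| *w* | R | True size | Interval too short by (1 - 1/R) |
|---|---|---|---|
| 0 | 1.00 | 5.0% | 0 |
| 0.5 | 1.06-1.07 | 6.4-6.6% | about 6% |
| 1 | 1.12-1.13 | 7.9-8.2% | about 10-11% |

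A linear time term in place of categorical periods gives the same values.

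**Step 3: size with variances estimated, as they will be in practice.** Simulation with a linear time term and Wald Z. The linear model used 3000 runs per scenario. The logistic model used 4000, with between-unit variance 0.125 on the logit scale (0.125 × 0.24 = 0.03).

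| Model | *w* = 0 | *w* = 0.5 | *w* = 1 |
|---|---|---|---|
| Unit only, linear, REML | 6.6% | 7.7% | 10.9% |
| Unit only, linear, ML | 7.5% | 8.9% | 11.9% |
| Unit only, logistic | 6.3% | 9.0% | 12.1% |
| Unit in hospital, linear, REML | 6.0% | 6.1% | 6.3% |
| Unit in hospital, linear, ML | 6.9% | 7.3% | 7.3% |

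At *w* = 0 the missing hospital term does no harm, so the excess over 5% there (roughly 1 to 2 points, 2.5 in the ML fit) is due to a Wald Z test with few clusters. With t on 8 degrees of freedom, the nested linear model rejects 2.4-3.7% of the time. With 16 degrees of freedom, it rejects 4.0-5.4%.

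**Step 4: power of the nested model at 1492 events, Wald Z.** With total variance 0.24, the SE is 0.0400-0.0402 at *w* = 0.5 (power about 78%) and 0.0412-0.0416 at *w* = 1 (75-76%). Across variance conventions, the ranges are about 76-78% and 73-76%.

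A t reference costs more. From the noncentral t with noncentrality 0.11/SE and total variance 0.24:

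| Reference | *w* = 0 | *w* = 0.5 | *w* = 1 |
|---|---|---|---|
| t, 8 df (critical value 2.306) | 72% | 67% | 64-65% |
| t, 16 df (critical value 2.120) | 77% | 73% | 70-71% |

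**The case against.** **No inflation is shown to exist.** A reader might infer that the interval is too short and that the trial's type I error is 11%. The documents do not support that. They give no hospital-level correlation, and with none the omission is harmless. The 11-12% figure needs the units of a hospital not to differ at all, and it includes the Wald Z excess. This objection stands, and the point is therefore conditional.

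**Evidence of correlation.** A reader might take the remark about staff covering shifts in another unit as proof that outcomes correlate within a hospital. The protocol offers it only as one route by which contamination could occur. It says nothing about shared leadership, post-arrest care or case mix. The planned covariates may also absorb some shared case mix, which the unadjusted calculations ignore. All this limits what can be said about size, but it does not justify assuming zero correlation.

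**Layout.** The units per hospital are a planning assumption for the fixed arms and are not given for the hospitals that cross over. The fixed hospitals also inform the time trend, so their data are not purely a comparison between hospitals. Both points stand as limits on precision.

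**Deliberate choice.** The protocol openly says that it randomises hospitals and analyses units, so this is not an oversight. But the reason given, contamination, explains the level of randomisation and not the omission of hospital from the model.

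**Left to the analysis plan.** This would count if the article were silent. It fixes the unit as the cluster for the planned analyses and names the single random effect.

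**Conclusion.** The point holds in conditional form. The primary analysis omits the randomised cluster and relies on zero within-hospital correlation beyond the unit effect, which the protocol never justifies.

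At a total ICC of 3% and the assumed layout, the omission alone, with variances known, raises the true size from 5% to about 6.5% if half the clustering is shared within hospitals and to about 8% if all is. With estimated variances and Wald Z, the corresponding figures are about 8-9% and 11-12%, including about 1-2 points from the few-cluster problem. The direction is certain if any hospital component exists; the amount is not known from the documents.

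**What to change.** In the Statistical analysis section, replace the unit-only sentence with: 'Hospital, and unit nested within hospital, will be included as random effects.' Keep the hospital effect even if the unit component is estimated as zero, because hospital is what was randomised. Test the treatment effect against a small-sample reference, for example t on about 8 degrees of freedom, in place of Wald Z. In the simulations 8 was conservative and 16 was close to 5%, so the choice should be fixed in advance and checked by simulation on the actual units per hospital.

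In the Sample size calculation section, restate the claim of more than 80% power as depending on the hospital-level correlation.

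The cost is a wider interval and lower power, as set out in steps 3 and 4 of the working. The loss is about 4 to 7 points under Wald Z, and more under a t reference. No extra enrolment or data are needed to make the change.

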### Data and safety monitoring

The NHLBI appointed an independent data and safety monitoring board (DSMB) to monitor study progress, adherence to the protocol, participant safety, and efficacy. The DSMB has initially planned to meet after the first, second, and third years of enrollment. Formal efficacy monitoring is not planned until after the second year, owing to the sigmoidal growth of the information fraction for TSW and HSW designs and because very early trends may not be representative. In particular, TSW and HSW designs have many more subjects enrolled in the control group than in the intervention group at interim time points. However, efficacy monitoring remains important to allow early stopping and dissemination of results in case of a very large intervention effect, as was observed in the single-center pilot study [19]. Efficacy monitoring will be conducted with the Lan-DeMets approach for flexible alpha spending [41], using conservative O’Brien-Fleming boundaries for early stopping [42].

## Discussion

More than half of the children experiencing an in-hospital cardiac arrest will die prior to hospital discharge [2–4]. Achieving recommended targets for chest compression rate, depth, and limiting interruptions in CPR have all been associated with cardiac arrest outcome [6, 7, 43–47]. However, several studies have demonstrated that even health care providers have difficulty meeting these metrics during real-life resuscitations [10, 48–52]. CPR quality is variable, and standard training courses have demonstrated limited success [5, 10–13]. In short, conventional training methods are failing.

However, there is preliminary evidence suggesting that structured debriefings for the entire care environment may improve outcomes. In particular, a single-center before-and-after pilot study showed an improvement from 29% to 50% in survival with favorable neurologic outcome [19]. These impressive findings have been highlighted by the Institute of Medicine as an exciting approach that should be disseminated to improve outcomes for the > 200,000 adults and children with in-hospital cardiac arrest in the United States each year [53]. Nevertheless, it is important to validate the results of the small, single-center before-and-after study in a larger multicenter trial.

If the results from the single-center pilot study are found to be generalizable, it will have a profound effect on CPR training and quality improvement initiatives, resulting in improved outcomes for children and their families. Assuming roughly 6000 pediatric in-hospital arrests annually [54] and an 11-percentage-point increase in the rate of survival with favorable neurologic outcome, the successful completion of this trial and national dissemination may save the lives of more than 600 children annually.

A TSW design is a relatively new, pragmatic trial design that is now frequently used to assess the effect of an intervention on a community. The HSW design is similar but often provides more power [21, 39], especially when transition periods are essential. To our knowledge, ICU-RESUS is the first implementation of an HSW design. The ICU-RESUS trial uses an HSW design with short transition periods to reduce the sample size, study duration, and cost. The transition period in the single-center pilot was 6 months, with debriefings held every 6–8 weeks. However, we found that these long transition periods had a detrimental effect on power for HSW designs and especially for TSW designs. Using a shorter but more intense transition period (3 months instead of 6 months with debriefings held every 4 weeks) and using an HSW design rather than a TSW design allowed the duration of the trial to be reduced from 6 years to 4.5 years, with accompanying reduction in sample size and cost. The effect of transition duration is so striking because the most influential observations are those immediately prior to and after crossover. Therefore, when a period of transition is included, the observations containing the most statistical information are lost. The effect is somewhat subdued in an HSW design because some hospitals do not cross over and therefore do not experience a transition. Nevertheless, transition periods for both TSW and HSW trials should be as short as possible while still allowing the effect of the intervention to be fully realized. This was achieved in ICU-RESUS by increasing the intensity of the intervention during the transition with more frequent debriefings, which allowed the transition period to be reduced from 6 to 3 months.

Most of the challenges of implementing an HSW trial are the same as for a trial with a TSW design. However, an HSW design introduces a few unique challenges, including the logistics of implementing an intervention prior to the start of enrollment and institutional willingness to participate. In a TSW trial, the intervention is first applied after a period of enrollment. In an HSW design, some hospitals must start the intervention prior to the enrollment period. This can add to the logistical complexity of study startup. When a transition period is required, such as in the ICU-RESUS trial, the start of enrollment may be delayed until the first hospitals are fully transitioned and ready to enroll in the intervention group. If the timeline is inflexible, enrollment may need to begin before the first hospitals have completed the transition to the intervention, reducing statistical power.

Another potential challenge that is unique to an HSW trial is that hospitals may not be willing to participate in a trial in which they might never have the opportunity to apply the seemingly beneficial intervention. However, if true equipoise exists, there should be no preconceived expectation that receiving the intervention will ensure better outcomes. This issue required substantial discussion, but all investigators and sites agreed that the results of the small, single-center before-and-after pilot do not support a generalizable conclusion about the effect of the intervention or justify broad application of this resource-intensive intervention without further study. Therefore, no reservations were expressed by investigators or by the institutional review board in regard to the study design. To assuage potential concerns that the remaining control hospitals may be deprived of this potentially lifesaving program, the investigators determined a priori that support will be provided for the implementation of the intervention, after trial completion, at those remaining control hospitals if it proves to be effective.

In conclusion, the ICU-RESUS trial uses a pragmatic and innovative design to determine whether structured debriefings coupled with point-of-care bedside practice can provide the much-needed improvement in pediatric resuscitation outcomes. This trial has the potential to profoundly impact pediatric in-hospital resuscitation outcomes as well as training and quality improvement initiatives. Additionally, our ongoing experience in the implementation of this trial may serve as an example to others of the practical benefits and challenges of using an HSW design.

